### Study design

The study is a monocenter randomized controlled trial comparing groups of pediatric cancer patients undergoing an overshadowing treatment during chemotherapy or receiving a placebo treatment. Figure 1 shows the study design.

**Figure 1 F1:**
[figure not shown]
Study design and flow of participants.

Different diagnoses require different cytostatics. Drugs, in turn, influence the probability of usage and the type of antiemetics. Block randomization will therefore be conducted within each diagnosis (that is, within the group of patients suffering from acute lymphoblastic leukemia or those suffering from Ewing’s sarcoma, and so forth). According to the recommendations of Altman and Bland [38], separate block randomization lists for each stratum will be used. This process is carried out by an independent third person not involved in data collection, analysis or medical care.

Participants, medical staff and data analysts will be kept blinded towards allocation. While blinding of medical staff and data analysts is easily realized, participants may notice if they get candy with a salient taste (experimental group) or without (control group). However, as the study information leaflets do not refer to taste in particular but to the effect of melting something in one’s mouth, they are not able to conclude their group allocation by their intervention. Accordingly, participants can also be considered blinded.

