**Methods/Design:**

Fifty-two pediatric cancer patients will be evenly assigned to two groups: an experimental group and a control group. The participants, hospital staff and data analysts will be kept blinded towards group allocation. The experimental group will receive during three chemotherapy cycles a salient piece of candy prior to every infusion, whereas the control group will receive flavorless placebo tablets.

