### Anticipatory nausea and emesis

As already mentioned, many cancer patients not only experience the side effects of nausea and emesis after chemotherapeutic drug infusion, but also prior to treatment [10]. These symptoms are known as ANV. The incidence ranges from 18 to 57% and nausea is more common than vomiting [5]. The reported rates vary widely among studies. Morrow and colleagues found in their meta-analysis of 35 studies an average prevalence of 29% for adult and pediatric patients [11]. Despite modern antiemetic treatment, ANV still occurs in 25 to 30% of cases [12].

The etiology of ANV can be explained by classical conditioning established by Pavlov (1849 to 1936). During conditioning an organism learns to associate an initial neutral stimulus (the conditioned stimulus) with a biologically relevant stimulus (the unconditioned stimulus). By pairing a conditioned stimulus with an unconditioned stimulus in the acquisition phase, the conditioned stimulus comes to evoke a conditioned response that is commonly similar to the response elicited by the unconditioned stimulus [13].

Accordingly, contextual stimuli of the clinic environment, such as the smell, sounds and sight of the building, function as the conditioned stimulus that becomes associated with the unconditioned stimulus of chemotherapy treatment. Following one or more contingent pairings (chemotherapy infusions), the patient may develop the conditioned response of nausea and/or vomiting even before the next treatment just by seeing the infusion, meeting the same clinician or already while re-entering the clinic [14].

As shown by Hickok and colleagues, the development of ANV coheres with the emetogenicity of the chemotherapy drug [15]. Beyond that, Tyc and colleagues showed that occurrence of ANV is positively correlated with severity of vomiting (intensity, frequency, duration) and number of chemotherapy cycles (conditioning trials) [16]. ANV is further inversely correlated with patient age, according to Morrow [17].

ANV is also seen in animal models. Limebeer and colleagues observe that, although rats do not vomit, they display a distinctive gaping reaction when exposed to a toxin-paired flavored solution [14]. After several pairings the contextual cues elicit a conditioned state of nausea in rats.

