### Sample size calculation

The calculation of the required sample size is oriented towards the demands of the first study question, which addresses the effect of overshadowing on ANV (primary endpoints). The effect sizes that were achieved in our pilot study for reduction of ANV are to be judged as very large in view of statistical conventions (effect sizes in *t* tests were *d* = 2.5 (nausea) and *d* = 1.4 (vomiting)). For the present study, a more conservative effect size of *f* = 0.4 in analysis of covariance (see below) is assumed. Aiming at a statistical power of 0.80, a total sample size of *n* = 52 is needed (two-sided α = 0.05).

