### Statistical analysis

The effect of the overshadowing treatment on both anticipatory (t1) and post-treatment nausea and vomiting, anxiety, quality of life and adherence (t2) will be analyzed using analysis of covariance comparing mean scores of intervention and control group while controlling for dosage of antiemetics. To account for different appropriate absolute dosages (mg/kg or mg/m^2^) among different patients and drugs, the variable dosage will be operationalized as the percentage of the recommended maximum dosage for each patient and drug. The assumed dependence between the prevalence of post-treatment (t2) and ANV (t1) will be determined by Pearson correlation coefficient.

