## Discussion

### Timetable

In consideration of the number of patients and the distribution of diagnoses in previous years, 23 patients per year in the study clinic would meet the inclusion criteria. Extrapolating this number leads to an inclusion period of approximately 2.5 years. If the number of participants is less than expected, the investigation will be extended to include a second center (a verbal commitment from University Clinic Lübeck was received). In that case the randomization procedure will be repeated in the second center. The trial is intended to start in summer 2013.

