### Limitations

Several limitations of this study have to be mentioned. First, it is unclear whether it will be possible to produce balanced study arms regarding diagnoses and antiemetics, respectively. In cases of clear imbalances, their impact on the result has to be discussed. Second, it is an open question whether overshadowing will work equally independently of age. Additionally, it is unclear whether ratings of ANV are influenced by the administering person (self-rating vs. third-person rating). However, our pilot study did not reveal any influence of age or application mode. Third, a paradox conditioning might occur: since nausea and vomiting are expected to occur closely after the application of candy, the latter might be associated with nausea and vomiting. Hence, both might occur as a consequence of other candy independently of treatment situations. However, this will not influence the desired effect on ANV as t1 lies before application of candy in the context of the third treatment cycle. Unintended induction of nausea and vomiting in patients’ everyday life is seen as unlikely since the tastes used as scapegoats are rather rare.

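### Randomisation is blocked within diagnosis, but the stated ANCOVA names only antiemetic dosage as covariate, so the test is conservative and precision is forgone if diagnosis is prognostic

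*Protocol article*

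**What the plan says.** Under Study design (text to Figure 1), the protocol article states "Block randomization will therefore be conducted within each diagnosis", using a separate list per stratum. The reason given is that diagnosis determines the cytostatics, and these influence whether and which antiemetics are used. Under Timetable, a second clinic may be added if recruitment falls short: "In that case the randomization procedure will be repeated in the second center".

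Under Statistical analysis, both anticipatory and post-treatment outcomes are to be analysed by analysis of covariance "comparing mean scores of intervention and control group while controlling for dosage of antiemetics". Dosage is expressed as a percentage of the recommended maximum for each patient and drug. No other covariate is named.

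The background section on anticipatory nausea and emesis links anticipatory nausea and vomiting (ANV) to the emetogenicity of the drug and adds that "ANV is further inversely correlated with patient age". Under Limitations, the article concedes that "it is unclear whether it will be possible to produce balanced study arms regarding diagnoses and antiemetics", and says that the impact of any clear imbalance will be discussed. The same section reports that the pilot study showed no influence of age.

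**The concern.** Blocking within diagnosis makes the arms more alike in diagnosis than simple randomisation would. If diagnosis predicts the outcome, the treatment difference then varies less from trial to trial than a model without diagnosis assumes. That model leaves the between-diagnosis variation in its residual, so it reports too large a standard error, and the test rejects less often than its nominal 5% under the null.

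The article gives grounds to expect diagnosis to be prognostic. Diagnosis fixes the drugs, the drugs differ widely in emetic risk (from under 10% to over 90% of patients across the classes described with Table 1), and ANV is said to follow emetogenicity. What is at stake is efficiency in a trial of 52 children: the stratified design would yield precision that the stated analysis does not collect.

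**Working it through.** **Inputs from the article.** N = 52, assigned evenly to two groups; "a more conservative effect size of *f* = 0.4 in analysis of covariance"; power 0.80; two-sided α = 0.05. For two equal groups, f = 0.4 corresponds to d = 2f = 0.8.

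**Step 1: the plan's own figure.** Two-group ANCOVA, noncentral F with λ = N·f² and df = 1 and N − 2 − (number of covariates).
- N = 52, one covariate: λ = 52 × 0.16 = 8.32, df = 1 and 49, power 0.807.
- N = 51, one covariate: power 0.799.

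So 52 is the smallest total that reaches 0.80. This holds with 0 to 3 covariates, and the stated sample size is reproduced.

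**Step 2: direction and limit of the standard-error effect.** Take outcome SD 1 and let R² be the share of variance explained by diagnosis. A model without diagnosis reports a standard error near 2/√N = 2/√52 = 0.277. With perfect 1:1 balance inside every diagnosis, the true SD of the estimate is 0.277 × √(1 − R²):
- R² = 0.2: 0.277 × √0.8 = 0.248.
- R² = 0.3: 0.277 × √0.7 = 0.232.

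Incomplete blocks leave some imbalance, so the true value lies between these figures and 0.277.

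**Step 3: simulation of the planned design.** Settings: N = 52, blocks of 4 within 5 or 8 diagnosis strata, 4,000 trials per setting. The planned model (arm + dosage) is compared with arm + dosage + diagnosis. Block size, number and size of strata, R² of diagnosis, and the dosage–diagnosis correlation (0 or 0.5) are assumptions, because the article gives none of them. In the rows with R² above 0, age is assumed to explain a further 10%. Ranges run over strata and correlations.

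| R² of diagnosis | Type I, planned | Type I, + diagnosis | Power at d = 0.8, planned | Power, + diagnosis |
|---|---|---|---|---|
| 0 (8 strata) | 0.048–0.049 | 0.050 | 0.80 | 0.77–0.78 |
| 10% | 0.036–0.047 | 0.046–0.054 | 0.80–0.82 | 0.82–0.83 |
| 20% | 0.033–0.040 | 0.049–0.054 | 0.81–0.84 | 0.85–0.88 |
| 30% | 0.023–0.035 | 0.046–0.054 | 0.83–0.85 | 0.90–0.92 |

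With dosage unrelated to diagnosis, the planned model's mean standard error is 0.28 against a true SD of about 0.26 (R² = 20%) and 0.24 (R² = 30%). The Monte Carlo standard error of a 5% rate is √(0.05 × 0.95/4000) = 0.003.

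The stronger the link between dosage and diagnosis, the smaller the effect. With ten assumed diagnoses and correlation 0 / 0.5 / 0.7, type I error under the plan is 0.033 / 0.039 / 0.047 at R² = 20% and 0.026 / 0.033 / 0.045 at R² = 30%.

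**Step 4: formula check on the gain.** With five strata, df2 = 52 − 2 − 1 − 4 = 45 and λ = 8.32/(1 − R²), where R² is now the share of the remaining variance explained by the added terms:
- R² = 0: λ = 8.32, power 0.81.
- R² = 0.1: λ = 9.24, power 0.85.
- R² = 0.2: λ = 10.40, power 0.88.
- R² = 0.3: λ = 11.89, power 0.92.

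With ten strata (df2 = 40) the figures are 0.80 / 0.84 / 0.88 / 0.92. At R² = 0 the formula shows less than one point of loss. The simulation shows more (for example 0.7975 to 0.7702, or 2.7 points, with 8 strata), because incomplete blocks leave arm and diagnosis slightly correlated.

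**Step 5: age.** Age is not a stratification factor. With age alone prognostic (R² = 20%, 8,000 trials), the planned model's standard error is 0.279 against a true SD of 0.275, and type I error is 0.045. Its omission leaves the standard error essentially right. It costs precision only: by formula, power would rise from 0.807 to 0.885 if age were added.

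**The case against.** The best defence is that the stated model already addresses the authors' reason for stratifying. They block by diagnosis because diagnosis affects antiemetic use, and they adjust for antiemetic dosage. If dosage tracks diagnosis closely, little is left over, and the simulation with correlation 0.7 shows type I error back near 5%. This stands as a limit on the size of the effect. It does not remove the point: dosage is scaled as a percentage of the recommended maximum for each patient and drug, so it measures antiemetic dose intensity rather than the emetogenicity of the chemotherapy.

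A second defence is that an article may leave covariates to a fuller document. But it does name the model and its covariate, and the mismatch lies in what it names.

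A reader might infer more than the documents support:
- **That the standard error is wrong in any general sense, or that false positives increase.** The error is one-sided (too large), and arises only so far as diagnosis predicts outcome beyond dosage. If diagnosis is not prognostic, the planned test is correct.
- **That the trial is underpowered.** It is not: N = 52 reproduces, and the planned model keeps about 80% or more at f = 0.4.
- **That omitting age is part of the same fault.** Age is not a stratum, and the article is divided on it: the background reports an inverse relation with ANV, while Limitations reports no influence in the pilot and leaves the question open.
- **That the lists should be redrawn by emetic-risk class.** Table 1 classifies drugs, not patients or regimens. The article gives no diagnosis shares or block size from which to compute how sparse the lists would be.
- **That a centre term is already missing.** The trial is planned in one centre; the second is a contingency.

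**Conclusion.** The point holds as a matter of efficiency, not validity. The design blocks on diagnosis and the stated ANCOVA does not include it. If diagnosis explains 20–30% of outcome variance, the planned test runs at about 2–5% instead of 5%. Its power at f = 0.4 is about 0.81–0.85, where the same data with diagnosis in the model would give about 0.85–0.92. The low end of the type I range needs dosage to be unrelated to diagnosis. If diagnosis has no prognostic value, nothing is wrong with the planned model, and the added terms would cost about 1–4 points of power.

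The mismatch and its direction follow from the article alone. The size depends on the assumed R², number of strata, block size and dosage–diagnosis correlation, so it is a range and not a single figure.

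**What to change.** In the Statistical analysis section, prespecify diagnosis (the randomisation stratum) as a factor in the ANCOVA alongside antiemetic dosage. With 52 patients, some diagnoses may be too rare to fit separately, so state a rule for grouping sparse ones and fix it before unblinding. Add centre as a factor if the second clinic opens. Age may be listed as an optional prespecified precision covariate, and should be described as that and no more.

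The cost is a few lines of text and one degree of freedom per added group (four for five diagnosis groups, one more for a second centre). Diagnosis is known for every patient because it is needed to randomise, so no new data are required. The randomisation lists and sample size stay as they are, and the trial status is given as ready to start recruitment, so the change can be made before any data exist.

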### Intervention

In the mentioned pilot study the overshadowing treatment known from the paradigm of classical conditioning was tested on pediatric cancer patients. To increase efficiency and applicability, an overshadowing technique known from Broberg and Bernstein will be used [34]. Implementing overshadowing in the hospital’s daily routine requires easy handling and regard to the high hygienic standards on the oncology ward, although in the proposed study the experimental group will receive salient candy and the control group flavorless placebo tablets instead of drinks. During three chemotherapy cycles the experimental group will get their treatment (candy) prior to each infusion. To avoid influences of possible aversive taste reactions, the flavor of candy will be changed from infusion to infusion.

Determining an evaluation period of three cycles can be seen as a compromise. On the one hand, more cycles may increase the intervention effect compared with the placebo condition. On the other hand, more cycles also increase the danger of withdrawals, missing data and comparability of participants and their treatment as the total number of treatment cycles differs widely between low-risk Hodgkin lymphoma and Ewing sarcoma, for example. Three cycles are thus a trade-off between a large effect size and threatened data quality. The pilot study [37] and the basic research [39] showed that even less than three cycles – where each comprises several unconditioned stimulus–conditioned stimulus pairings – is sufficient. However, to determine the applicability of the intervention in daily clinical routine (the third subgoal), the overshadowing treatment in the experimental group will be continued until the end of treatment without any further outcome assessment whenever possible.

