### Measures

#### Measuring nausea and vomiting

Symptoms of nausea and emesis will be measured using discomfort logs administered by patients. These logs have been successfully used in our pilot study [37]. They assess nausea and vomiting on 6-point Likert scales focusing on intervals of 2 hours, thus leading to 12 ratings every day. Children from 4 to 7 years of age will be interviewed by a blinded interviewer about their symptoms, and also parents will be asked about their observations. Children from the age of 8 years will use a self-assessment version.

As a second measure, the combined nausea and vomiting scale Baxter Retching Faces (BARF) by Baxter and colleagues will be used [40]. BARF uses a 6-point visual analogue scale with six comic faces expressing mimics ranging from neutral mood to vomiting. The authors developed the BARF scale for children aged from 4 to 17 years. The validation study confirms reliability and validity among patients from 7 to 18 years old. In our study, the BARF scale will be administered by all patients.

There will be two measurement points: the anticipatory measurement phase prior to the third chemotherapy cycle, and also the post-treatment phase after the third chemotherapy cycle (see Figure 1 and Table 4).

**Table 4 T4:** Planned measurements for study aims and subgoals

**Measurement**	**Pre-chemotherapy cycle 3 (anticipatory), t1**	**Post-chemotherapy cycle 3, t2**
Nausea and vomiting (discomfort log, BARF)	X	X
Anxiety (KAT-II, STAI)	X	
Quality of life (Kiddy-KINDL, Kid-KINDL, Kiddo-KINDL)		X
Adherence (caregivers and physicians questionnaires)		X

*BARF*, Baxter Retching Faces; *KAT-II*, Kinder-Angst-Test (Children Anxiety Test); *KINDL*, German Children's Quality of Life Questionnaire (Kiddy/Kid/Kiddo version for each age group); *STAI*, State and Trait Anxiety Inventory.

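### The plan calls participants blinded to allocation, but they can taste which product they get; the leaflet masks at most the hypothesis, so bias in patient-rated outcomes cannot be excluded

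*Protocol article*

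**What the plan says.** The abstract (Methods/Design) says: "The participants, hospital staff and data analysts will be kept blinded towards group allocation". The Study design section, in the text under Figure 1, repeats it: "Participants, medical staff and data analysts will be kept blinded towards allocation". The same paragraph then concedes that "participants may notice if they get candy with a salient taste (experimental group) or without (control group". It sets this aside "as the study information leaflets do not refer to taste in particular but to the effect of melting something in one’s mouth", infers that "they are not able to conclude their group allocation by their intervention", and ends: "Accordingly, participants can also be considered blinded".

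Under Intervention, "the experimental group will receive salient candy and the control group flavorless placebo tablets instead of drinks", and the candy's flavor varies between infusions.

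On outcome assessment, "Symptoms of nausea and emesis will be measured using discomfort logs administered by patients" (Measuring nausea and vomiting). Patients aged 8 and over rate themselves. Those aged 4 to 7 are questioned by a blinded interviewer, and their parents' observations are also collected. All patients complete the BARF scale. The anticipatory rating (t1) is made before cycle 3.

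**The concern.** Blinding to allocation means that a person cannot tell which intervention was received. The plan concedes that the product can be recognized, then argues from what the leaflet leaves out. That argument addresses a different property: whether the participant knows which product is thought to be active. The plan treats the two as the same.

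The difference matters because the primary outcome depends largely on patients' own reports, and the section on post-treatment nausea and emesis lists the patient's expectation of these effects among the risk factors. If the two products raise different expectations, symptoms or their reporting could differ between arms without any overshadowing effect. A reader who accepts the blinding statement would discount that explanation. The Limitations section does not mention it.

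**Working it through.** **1. What the stated safeguard can support**

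| Question | What the protocol article says | What follows |
|---|---|---|
| Can the products be told apart? | Salient candy of changing flavor against a flavorless tablet (Intervention); participants may notice (Study design) | The product is perceptible |
| Are participants told that taste is the active element? | No; the leaflet speaks of melting something in the mouth (Study design) | The hypothesis is masked, as far as the leaflet goes |
| Can they still infer their group? | Asserted that they cannot; the article describes no check | Untested; a flavorless tablet may be guessed to be the placebo |
| How much exposure precedes the primary rating? | t1 is before cycle 3 (Table 4) | Two cycles of tasting the product |
| Who supplies the rating? | Self-rating from age 8; blinded interviewer plus parents at ages 4 to 7; BARF by all patients | Mainly the patient; at 4 to 7 the child remains a source |
| Is expectation relevant to the outcome? | Named as a risk factor (Background) | A route for bias exists on the plan's own account |
| Is it listed as a limitation? | No | The reader is not warned |

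The step from masked hypothesis to blinded allocation does not follow.

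**2. The plan's own figure**

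The point does not depend on sample size, but the figure was checked because the illustration below uses it. Inputs from Sample size calculation: f = 0.4, power 0.80, two-sided α = 0.05, total 52; the abstract gives even assignment, so 26 per arm. With one covariate the denominator df is 52 − 3 = 49 and the noncentrality is f² × N = 0.16 × 52 = 8.32. The noncentral F distribution gives power 0.807. N = 50 gives 0.791, so 52 is the smallest even total that reaches 0.80. The stated figure is reproduced.

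**3. Illustration of size (assumed shifts)**

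The documents give no size for an expectation or reporting effect. Let b be an assumed shift between arms in SD units, with no true effect. The noncentrality is b / √(2/26) = b / 0.2774 on 49 df, and an observed difference of about 0.56 SD is significant.

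| Assumed b (SD) | Noncentrality | Probability of p < 0.05 |
|---|---|---|
| 0 | 0 | 0.050 |
| 0.1 | 0.36 | 0.064 |
| 0.2 | 0.72 | 0.109 |
| 0.3 | 1.08 | 0.186 |
| 0.4 | 1.44 | 0.293 |
| 0.5 | 1.80 | 0.424 |

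The direction is equally unknown. The planned f = 0.4 corresponds to d = 2 × 0.4 = 0.8. If a shift worked against the candy, the net difference would be 0.6, 0.5 or 0.4 SD for shifts of 0.2, 0.3 or 0.4, and power would fall from 0.807 to 0.564, 0.424 or 0.293 by the same calculation.

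**The case against.** The strongest defense is that the intervention is a salient taste, so participants cannot be kept from perceiving it, and that the plan discusses this openly. Both arms melt something in the mouth under the same neutral information, so each has been given a plausible reason to expect benefit. Expectation bias needs participants to believe that one product is the active one, and the leaflet targets exactly that belief. In addition, a blinded interviewer collects the ratings at ages 4 to 7, and vomiting can be observed.

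Much of this stands. The safeguard is real and should be credited. It does not rescue the stated conclusion, because it masks the hypothesis, and its success is asserted rather than checked.

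A reader might infer more than the documents support:

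- **That the design offers no protection.** The common leaflet gives some.
- **That bias favors the candy.** The direction is not shown. The plan itself raises aversive taste reactions (Intervention) and the candy becoming associated with nausea (Limitations), which could act the other way.
- **That staff are unblinded.** This would need a visible difference between products. The article states none, and it may leave appearance and packaging to the full protocol. That families compare products on the ward is likewise conjecture.
- **That continuing candy in one arm after cycle 3 contaminates the ratings.** The Intervention section plans no outcome assessment during that continuation, and Table 4 ends at t2.

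**Conclusion.** The statement that participants are blinded to allocation is stronger than the design delivers. What the plan supports is that participants are not told the hypothesis while the product is perceptible, a protection that is partial and untested. Since the primary ratings come mainly from patients and the plan itself treats expectation as a risk factor, expectation or reporting bias cannot be excluded, and the trial should not be reported as participant-blinded.

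Neither the presence, the direction nor the size of such bias can be established from the documents. The false-positive rates of 11%, 19% and 29% show only what shifts of 0.2, 0.3 and 0.4 SD would do if they existed; they are not estimates for this trial. The correction concerns a claim and a missing check. It gives no reason to change N or the primary analysis.

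**What to change.** 1. In the abstract and in Study design, replace the blinding claim for participants and parents with wording such as: *not told the study hypothesis; the product received is perceptible*. Keep the claim for interviewers and data analysts.
2. Describe the control in one way throughout. Study design implies candy lacking a salient taste, whereas the abstract and Intervention say flavorless placebo tablets.
3. Ask participants or parents which product they think they were allocated and how much benefit they expect, in the same neutral words in both arms. Do this close to the t1 rating, ideally before it: asking at t2 would follow the primary outcome and mix the guess with perceived benefit. Report the answers descriptively as exploratory. Do not treat results split by guess as a correction for bias. Even at t1 the guess follows randomization and two cycles of symptoms, so a true effect could influence it.
4. Add perceptible allocation to Limitations, with a note that direction and size are unknown.

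The cost is a less favorable blinding statement, some rewording and two short questions.
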